**Methods:**

A multicentre prospective cohort study (FemCure) is set up in which genital and/or anorectal CT positive women (*n* = 400) will be recruited at three large Dutch STI clinics located in South Limburg, Amsterdam and Rotterdam. The women self-collect anorectal and vaginal swabs before treatment, and at the end of weeks 1, 2, 4, 6, 8, 10, and 12. Samples are tested for presence of CT-DNA (by NAAT), load (by quantitative polymerase chain reaction -PCR), viability (by culture and viability PCR) and CT type (by multilocus sequence typing). Sexual exposure is assessed by online self-administered questionnaires and by testing samples for Y chromosomal DNA. Using logistic regression models, the impact of two key factors (i.e., sexual exposure and alternate anatomic site of infection) on detection of anorectal and genital CT will be assessed.

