### Study population

The eligible study population is likely to reflect the current STI clinic populations. Eligible are heterosexual women with symptomatic or asymptomatic genital and/or anorectal CT infection, who are not pregnant and 18 years or older. Exclusion criteria are recent reported use of antibiotics, HIV positivity, syphilis and infection with *Neisseria gonorrhoea*. As single anorectal CT is uncommon and around 75-95 % of genital CT positive women also have anorectal CT [13–25], it is expected that of the included women only few will have anorectal CT only. The majority (75 %) expectedly will have anorectal CT in combination with genital CT, and most of the remainder will have genital CT only at inclusion in the study. Treatment occurs according to regular care and international guidelines [35–37]. Women who are anorectally tested in routine care and found anorectal CT positive are treated with a 7-day course of doxycycline 100 mg twice daily with the first dosis being directly observed. All other women receive a directly observed single dose of azithromycin 1000 mg [35–37]; these women tested genitally CT positive in routine care and were either anorectally untested in routine care or were tested anorectally CT negative.

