### Defining alternate anatomic site exposure

The process of CT anorectal acquisition from her own genital CT infection and vice versa is defined based on the CT test results. Exposure is defined as presence of CT detection at the other anatomic site at the same sampling moment and/or the previous sampling moment. CT typing results are also used to confirm the link between the two detections.

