	Sexual exposure and genital site exposure	Anorectal sexual exposure (at T_x_) AND genital CT positive (at T_x_ and/or T_x-2_)	Sexual transmission AND/OR Transmission from genital site

^a^Based on self-administered questionnaires and semen biomarker assessment

^b^T_x:_ test result at the sampling; T_x-2:_ test result at the sampling two weeks earlier

^c^Strain typing is used to further aid interpretation of the observed positive CT test result, specifically to confirm self-infection (i.e., strain types do not differ between anatomic sites) or persistence (i.e., strain types do not differ over time)

Risks will be expressed by odds ratio‘s and 95 % confidence intervals. Co-factors (such as age, but also treatment-type) will be included in the models to account for their potential role as a confounding factor or effect-modifier in the associations between exposure and CT detection. Also, these co-factors are assessed for their association with CT detection.

Sensitivity analyses will be undertaken by varying the definition of the outcome (primary and secondary outcomes) and by varying the definition of the sexual exposure (e.g., including and excluding sexual practices). By performing a (limited) process evaluation of our study, we will obtain insights in the factors that have affected participation and possible loss-to-follow-up.

In a sub analysis, in which the unit of analysis will be an individual woman (not the 2-week episodes), a head-to-head comparison of the two treatments will be conducted.

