### Numbers and power

Based on the power calculations we need to include 300 - 380 women with full retention, to be able to answer the main study question and the sub-analyses with sufficient power (at least 70 %) to show statistically significant (5 %) associations of a relevant size. This was calculated in different scenarios by varying the assumptions in number of women with full data (300–380), the percentage of CT detections (15-30 %), the percentage of reported sex during a 2-week episode (20-60 %) and the percentage of alternate anatomic site exposure (10-30 %). Accounting for women who are anorectally CT negative at inclusion, loss-to-follow up, missing data, and persistence, we need to recruit 400 women in the study to be able to have sufficient numbers of samples that can be analysed.

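### Alternate-site exposure is defined in two conflicting ways, and each lets the pre-treatment swab count as a post-treatment source at one early visit (week 1 or week 2)

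*Protocol article*

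**What the plan says.** The section Defining alternate anatomic site exposure states: "Exposure is defined as presence of CT detection at the other anatomic site at the same sampling moment and/or the previous sampling moment". Table 2, under Statistical analyses, gives the main regression models. It counts the other site as exposed if positive at T_x and/or T_x-2, and footnote b explains T_x-2 as the "test result at the sampling two weeks earlier".

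According to the abstract, swabs are taken "before treatment, and at the end of weeks 1, 2, 4, 6, 8, 10, and 12". On entry, Study population says: "Eligible are heterosexual women with symptomatic or asymptomatic genital and/or anorectal CT infection". It expects this mix: "The majority (75 %) expectedly will have anorectal CT in combination with genital CT, and most of the remainder will have genital CT only".

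Under Definition of transmission, a positive sample that follows a positive sample is treated as possible persistence, not transmission. In Model 2 of Table 2, a detection with the other site positive and no sexual exposure is read as transmission from that site. With sexual exposure it goes to a mixed row. Persistence is the reading only in the row with neither exposure.

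**The concern.** The study sets out to separate sexual transmission from self-infection after treatment. Alternate-site exposure is one of its two key exposures, so it has to be defined once and has to describe a possible source after treatment. A positive T0 swab describes an infection that was then treated. It is also the reason the woman is in the cohort, so using it as exposure makes exposure nearly universal at that visit.

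Two things are at stake. Detections soon after treatment may be read as cross-site transmission when residual DNA or persistence would explain them equally well. And early visits, where residual detection is highest, enter the pooled model almost wholly on the exposed side.

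**Working it through.** **1. Which swab each rule reaches.**

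| Sampling | Text: previous sampling | Footnote b: two weeks earlier |
|---|---|---|
| Week 1 | T0 | no sample |
| Week 2 | week 1 | T0 |
| Weeks 4 to 12 | two weeks earlier | two weeks earlier |

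Neither rule reaches T0 at both early visits; each reaches it at one. Nothing in the article bars this.

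**2. Inputs.** Dual-site share B = 75% (Study population). Anorectal-only share a = 1-5%, my reading of few. Genital-only share g = 25% − a = 20-24%. Planned recruitment is 400. The only exposure frequency the article gives is the 10-30% under Numbers and power. It has no derivation and no week attached, so it cannot be reproduced.

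**3. Week 1, text rule.** A site is at risk if negative at T0. An eligible woman negative at one site is positive at the other, so she is exposed.
- Anorectal outcome: 400 × 0.20 to 400 × 0.24 = 80-96 women at risk, all exposed.
- Genital outcome: 400 × 0.01 to 400 × 0.05 = 4-20 women at risk, all exposed.
- Exception: women whose T0 study swabs are negative at both sites, which can happen because recruitment follows an earlier routine positive.

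**4. Week 2, Table 2 rule.** Let at risk mean negative at week 1, and let q be the chance that a site positive at T0 is negative at week 1 (assumed 0.2-0.8, the same whatever the other site's T0 status). Counting exposure from T0 alone:
- Genital outcome: (qB + a) / (q(B + g) + a). With a = 0.01, q = 0.8: 0.610/0.802 = 76%. With a = 0.05, q = 0.2: 0.20/0.24 = 83%.
- Anorectal outcome: (qB + g) / (q(B + a) + g). With a = 0.05, q = 0.8: 0.80/0.84 = 95%. With a = 0.01, q = 0.2: 0.390/0.392 = 99%.

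Positives at T_x can only add to these shares. The article also states that "around 75-95 % of genital CT positive women also have anorectal CT"; with B = 95% the genital share rises to about 96-100%. If at risk meant negative two weeks earlier, the share would be 100% for both outcomes, as in step 3.

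**5. How far the rules differ at week 2.** A simulation assumed 75/20/5% dual, genital-only and anorectal-only infection, residual positivity of 50% then 20%, or 70% then 40%, at weeks 1 and 2, and 3% new detection per interval. Under the text rule 51-69% (genital) and 60-80% (anorectal) are exposed, against 81-83% and 96-97% under Table 2. Between 14% (83 − 69) and 36% (96 − 60) of at-risk women change category with the rule chosen.

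**6. What this does to a label.** Take a woman positive at both sites at T0, negative at both at week 1, and anorectally positive but genitally negative at week 2, with no anal sex. Under Table 2 she is transmission from the genital site. Under the text rule she has neither exposure and is read as persistence. In the same simulation with no cross-site effect, 94% of week-2 incident anorectal detections fall in the exposed rows under Table 2.

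**7. Pooled odds ratio.** The simulation was extended to week 12 with residual positivity of 5-15% at week 4 falling to 0 by week 10, and 20% clearance of new infections per interval. With a true odds ratio of 1, the Table 2 rule gives about 2.3-2.6 without a week term and 0.93-0.97 with one. This needs residual detection to be intermittent, so that a treated site can test negative and then positive again. If a cleared site stays negative, the null odds ratio remains near 1.

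**8. Safeguards in the article.** Strain typing covers a subset and reads the same strain as self-infection across sites or persistence over time, so it cannot separate the two in a dual-site woman. Viability testing is at T0 and weeks 4, 8 and 12. The sensitivity analyses vary the outcome and the sexual exposure, not alternate-site exposure.

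**The case against.** The best defence is that the problem is confined to the start of follow-up and largely handled by ordinary modelling. Week 1 may not be a model episode at all: the unit is a two-week episode, and the week-1 questionnaire covers sexual behaviour only briefly. A journal article may leave that, and a week term, to the full plan. With a true odds ratio of 3, week-adjusted estimates are 1.5-2.0 under Table 2, 1.5-1.8 under the text rule and 1.7-2.1 when starting at week 4. The look-back choice then matters little, and no option recovers 3.

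Much of this stands, and it rules out four stronger readings that a reader might infer.
- That exposure is far outside the 10-30% used for power. Pooled over all samplings under Table 2 it is 23-29% (genital) and 27-34% (anorectal), within or just above that range.
- That every early detection is booked as self-infection. A week-1 positive at a site positive at T0 counts as persistence, and detections with sex go to the mixed row.
- That the unexposed rows are empty at both weeks. At week 2 about 17-24% remain unexposed for the genital outcome under Table 2, and more under the text rule.
- That adjusting for time does not help. It removes most of the spurious pooled effect.

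What the defence does not answer is that both definitions are written down and disagree. If week 1 is left out, the Table 2 rule still takes week-2 exposure from T0. A week term corrects the pooled estimate but not the row-by-row interpretation in Model 2.

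**Conclusion.** The point holds in this limited form. One of the two main exposures has two incompatible definitions, and each counts a just-treated infection as a post-treatment source at one early visit. The conflict itself rests on the article's wording alone. The week-1 result also needs only eligibility, with the exception for women negative at both sites at T0. The week-2 shares of 95-99% (anorectal) and 76-83% (genital) rest on the 75% dual-site figure and an assumed 1-5% anorectal-only share.

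The pooled inflation is the least certain part: it requires intermittent residual detection and a model without a week term. The article names age and treatment type as co-factors and does not mention week, but it does not exclude it. The definitions should be reconciled before the episode models are run, because the same week-2 data can be read as self-infection or as persistence depending on the section followed.

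**What to change.** Put one rule in both the section on alternate-site exposure and Table 2, footnote b: other site positive at the same sampling and/or the previous post-treatment sampling. State that T0 never counts as alternate-site exposure, and state the at-risk set for each outcome. Report week-1 detections descriptively, outside Models 1 and 2. Let the week-2 episode use the week-1 swab, and run the models from week 4 as a sensitivity analysis. Name a week term in the models if the full plan does not already have one, since the new look-back alone does not remove confounding by time since treatment.

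The cost is wording in two places. The week-1 episodes leave the models, but they carry almost no exposure contrast and are still reported. At week 2 the look-back becomes one week while sexual behaviour still covers two, which should be noted beside the definition. The change does not cure the attenuation seen with a true odds ratio of 3.

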### Numbers and power

Based on the power calculations we need to include 300 - 380 women with full retention, to be able to answer the main study question and the sub-analyses with sufficient power (at least 70 %) to show statistically significant (5 %) associations of a relevant size. This was calculated in different scenarios by varying the assumptions in number of women with full data (300–380), the percentage of CT detections (15-30 %), the percentage of reported sex during a 2-week episode (20-60 %) and the percentage of alternate anatomic site exposure (10-30 %). Accounting for women who are anorectally CT negative at inclusion, loss-to-follow up, missing data, and persistence, we need to recruit 400 women in the study to be able to have sufficient numbers of samples that can be analysed.

## Discussion

The FemCure study will deliver information on the role of anorectal CT in the transmission of CT. It may guide further care-optimization for anorectal CT testing and treatment as in current care women are not routinely tested anorectally. It will also describe the microbiological specifics of genital and anorectal CT detection after treatment, such as on the viability of detected CT, which is relevant for clinical practice and for healthcare policy making in order to reduce avoidable transmission.

### Strengths

First, this study will generate new information on the meaning and the cause of CT detection after treatment. This information goes beyond current state of the art due to its combination of different laboratory tests (NAAT, viability, load, typing) to detect CT, and by sampling both anorectal and genital anatomic sites in the same woman and multiple points in time. Second, the recruitment at multiple STI clinics, serving ample numbers of clients, allows us to study sufficient numbers of patients in a relatively short time period. Naturally, our study domain is restricted to patients consulting a STI clinic, which we consider the relevant population for this research question. We do not expect that results would be different for clients consulting a general practitioner or gynaecologist for their CT infection. Third, the study nurses and the participants are blinded to the results of the laboratory testing as testing will be done in batches afterwards. All data will be handled coded, ensuring the anonymity of included patients. Fourth, several measures are taken to optimize reliability and validity of measures of sexual exposure, including the use of pre-tested questions using standard terminologies that people have shown to comprehend, computer-assisted self-interviewing, using short recall periods (2 weeks), and using an administration mode that ensures privacy. Also self-reports are validated by applying biochemical measures. Although the Y chromosome DNA may not be detected in all exposures, if it is detected it is used to capture underreporting and instances of incorrect condom use or condom failure. These biomarker analyses will be done on already collected swabs, thus no extra swab is needed from a participant. Fifth, the research team is interdisciplinary and highly experienced in CT research and covers the different areas of expertise needed to successfully conduct the proposed research. It consists of members several Dutch Public Health Services, STI clinics, Medical Microbiological Laboratories, Universities (including behavioural science), and national institutes for policy and STI guideline development ensuring the quality of the study and the valorisation, i.e., the practical implication of results.

### Limitations

First, it cannot be ruled out that some degree of misclassification in both exposures and outcomes may occur. Sexual exposure may be underreported, even when validity and reliability of the questionnaire data are optimized and biomarker validation is applied (exposure misclassification). Also, a woman may clear the CT infection before the sampling occurs (outcome misclassification). However, an even more frequent sampling as already scheduled (at weeks 0,1,2,4,6,8, 10, and 12) was considered to potentially compromise study inclusion and retention and would also require more funds than are currently available.

Second, a randomised controlled trial (RCT) would be the most suited study design to compare efficacy of treatments, such as recently reported for genital CT [48]. The observational FemCure study is not designed as an RCT as a treatment comparison is not its main aim and an RCT would require more human and financial resources than are currently available. Nevertheless, the role of treatment can and will be evaluated in a sub-analysis by a head-to-head comparison of treatment-types. Most of the current studies reporting comparison of anorectal CT treatments similarly are observational studies with inherent biases to account for [28–32, 39–41]. By including different anatomic sites and a diverse range of laboratory and exposure measures in the current study, results will add to the existing literature and will thereby be able to inform the current debate on treatment failure.

## Abbreviations

CT, *Chlamydia trachomatis*; DNA, deoxyribonucleic acid; MLST, multilocus sequence typing; NAAT, nucleic acid amplification test; PHS, public health service; STI, sexually transmitted infection
